### Measurement of drug concentrations

Samples collected for drug measurement are stored at −70 °C to −80 °C until analysis. Drug concentrations are measured using validated liquid chromatography mass spectrometry (LC-MS/MS) assays. All methods are being validated in accordance with the Clinical Pharmacology Quality Assurance and Quality Control Program (CPQA) method validation guidelines [19], which are required for analyzing study specimens within the Division of AIDS (DAIDS) HIV clinical trial networks (based on the US Food and Drug Administration Guidance for Industry Bioanalytical Method Validation [20]). This laboratory participates in two international External Quality Control (EQC) programs for quantification of antiretroviral drugs: (i) the HIV/AIDS Clinical Pharmacology Quality Assurance program from the University at Buffalo, NY, which performs standardized inter-laboratory testing twice a year [21], and (ii) ASQUALAB Quality Control program, France (http://www.asqualab.com/).

### Sample size calculation

The sample size is based on ensuring precision in pharmacokinetic parameter estimates to accurately describe the pharmacokinetics of TFV. Using the plasma pharmacokinetic parameters as a reference value, the precision required is a mean TFV plasma AUC_0-24h_ at steady state within ±25% of the true population mean. The mean (± standard deviation) TFV AUC_0-24h_ in HIV-infected adults is 3.32 ± 1.37 μg.hr./mL [coefficient of variation (CV) of 41.2%] following multiple doses of 300 mg once daily [13]. Assuming the true population mean plasma AUC_0-24h_ at steady state is the same for healthy subjects, the sample mean must fall within ±0.83 μg.hr./mL of the true mean to ensure 25% precision. Based on this variability, at the standard dose and assuming average AUC results are normally distributed, to be 90% confident that the plasma TFV AUC_0-24h_ sample mean is within 0.83 μg.hr./mL of the true mean, a sample size of 10 participants is required for each of the 3 groups, making 30 participants in total. Subjects who do not complete the study will be replaced.

### Statistical analysis

The primary endpoints are descriptive pharmacokinetics endpoints. A Kruskal-Wallis test will be used to compare basic demographic variables between the three groups. A non-compartmental pharmacokinetic analysis will be performed on the TFV concentration data generated from the intensive blood samplings at Week 7. Pharmacokinetic parameters in plasma and blood (venous and fingerstick) will include: area-under-the-curve (AUCτ), maximum concentration (C_max_), time to C_max_ (T_max_), apparent clearance (CL/F), apparent volume of distribution (V/F), and minimum concentration (C_min_). AUCτ will be determined using the linear trapezoidal method. C_max_, C_min_ and T_max_ will be taken directly from the observed concentration-time data. The terminal slope (λz) will be determined from the log-linear portion of the curve, and the half-life will be calculated as Log_10_ (2)/λz. Total body clearance (CL/F) will be calculated using Dose/AUC_0-τ_. The fraction of TFV excreted unchanged in the urine (Fe_TFV_) will be determined as the total amount of TFV excreted during the urine collection period following cessation of RDF divided by the dose. The renal TFV clearance (CLR) will be calculated by multiplying Fe_TFV_ and CL/F. We will calculate median (range), means (standard deviations), and geometric means with 95% confidence intervals for each PK parameter.

We will compare pre-dose TFV concentrations in specimens collected during the treatment lead-in period (i.e. before 2nd dose of TDF/FTC, and at Weeks 3, 5 and 7) using a Kruskal-Wallis test. We will report the time course of TFV washout in blood, plasma, urine and oral fluid based on the detected drug concentrations following drug cessation. We will perform non-pharmacokinetic statistical analyses using Stata (Version 10.0, StataCorp LP, Texas, USA).

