## Background

Daily oral tenofovir-based pre-exposure prophylaxis (PrEP) has been shown to be safe and effective in reducing the risk of HIV acquisition in adults [1–3]. Truvada®, composed of 300 mg of tenofovir disoproxil fumarate (TDF) and 200 mg of emtricitabine (FTC), is approved for PrEP by the US Food and Drug Administration [4] and is now recommended by the World Health Organization (WHO) for people at substantial risk of HIV infection as part of combination HIV prevention approaches [5]. TDF is also recommended by the WHO as part of first-line antiretroviral therapy (ART) and at the end of 2014 approximately 70% of people on first-line ART were taking a TDF-based regimen [6]. The efficacy of PrEP and ART, however, depend on adequate pill adherence to maintain sufficient drug concentrations [7]. Existing tools to monitor ART and PrEP adherence, such as patient self-reporting [8, 9], pill counting and home-based visits [9–11] have been shown to be ineffective. Electronic pill bottle caps/boxes are more accurate, but their high cost and complexity confine their utility to research settings. Real-time drug testing through simple, low-cost tools to identify poor PrEP or ART adherence would be valuable to help maintain the success of global HIV treatment and prevention programs.

TDF has favorable pharmacokinetic properties for an objective measure of drug adherence. TDF is a prodrug that is rapidly converted to tenofovir (TFV) after oral administration via esterase hydrolysis after absorption [12]. Once inside HIV-infected CD4 T cells, TFV is converted to its active form—TFV-diphosphate (TFV-DP) [12–14]. TFV has a plasma elimination half-life of 17 h and TFV-DP has an intracellular half-life in peripheral blood mononuclear cells (PBMCs) of 4.2 days [15]. An intracellular TFV-DP concentrations of >16 fmol/10^6^ PBMCs was associated with a 90% HIV risk reduction (EC_90_) in HIV acquisition and with ≥4 doses of TDF per week would yield TFV-DP concentrations in PBMCs associated with a 96% HIV risk reduction [7]. While the detection of TFV in plasma and TFV-DP in PBMCs have been proposed as objective measures of recent and cumulative drug adherence, respectively, the use of more accessible biological samples, such as fingerprick blood, urine, or oral fluid samples, would be preferable for real-time drug testing for adherence.

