### Intensive 24-h PK blood sampling phase

On the Monday morning of Week 7, a pre-dose blood sample is drawn and a single Truvada® tablet is administered by the study team on an empty stomach (with at least 6 h fast beforehand). This is the last dose of Truvada® for all subjects. Venous blood samples are then collected at 1, 2, 4, 6, 8, 10, 12 and 24 h post-dose. At each time point, a venous blood dried blood spot (DBS, 5 spots) and fingerstick DBS (2 spots) are collected. Oral fluid samples are collected at pre-dose, 1, 4, 12 and 24 h post-dose. Urine samples are collected pre-dose and over the intervals of 0–4 h, 4–8 h, 8–12 h, and 12–24 h. PBMCs are only collected pre-dose. Renal and liver function tests are performed for safety evaluations.

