### 4-week wash-out phase

After the intensive PK sampling is complete, subjects return to the clinic once a day for the remaining 5 days of Week 7 for blood, urine (24-h) and oral fluid specimen collection (Table 2).

Blood and urine are collected on Monday and Thursday of Week 8, and then on Monday morning of Weeks 9 and 10. Blood and urine are collected and a final blood chemistry is performed at the last study visit (end of Week 10) on the following Monday morning.

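### On its natural reading, the plan fits λz to the 24-hour intensive curve, less than one half-life of usable decline, although later blood samples are already scheduled

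*Protocol article*

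**What the plan says.** The Statistical analysis section names the data set: the non-compartmental analysis "will be performed on the TFV concentration data generated from the intensive blood samplings at Week 7". In the same paragraph, the terminal slope λz "will be determined from the log-linear portion of the curve", half-life is derived from λz, and V/F is among the listed parameters for plasma and for venous and fingerstick blood. No time window and no minimum number of points is given.

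The section titled "Intensive 24-h PK blood sampling phase" sets the schedule after the pre-dose sample: "Venous blood samples are then collected at 1, 2, 4, 6, 8, 10, 12 and 24 h post-dose". It also says of the Monday dose in Week 7: "This is the last dose of Truvada® for all subjects".

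The section on the 4-week wash-out phase continues: "After the intensive PK sampling is complete, subjects return to the clinic once a day for the remaining 5 days of Week 7 for blood". Table 2 schedules plasma and dried-blood-spot samples on Wednesday to Sunday of that week, nominally 48, 72, 96, 120 and 144 h after the last dose. The only use the Statistical analysis section states for the washout samples is a report of how concentrations fall after dosing stops.

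The Background gives the relevant time scale: "TFV has a plasma elimination half-life of 17 h".

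**The concern.** A terminal slope needs samples spread over enough of the decline for the fall to stand out from assay and sampling noise. The only curve named in the paragraph is the intensive one. It ends 24/17 = 1.41 half-lives after the dose, and the part usable for a terminal fit is shorter still. With samples at 8, 10 and 12 h and then one at 24 h, the fit is close to a line through an early cluster and a single late point.

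At stake are half-life and V/F. The usual V/F is CL/F divided by λz; the article gives no formula. Error in λz enters each subject's half-life and V/F, and so the standard deviations, ranges and confidence intervals promised for each parameter. No further dose follows, so the later samples show undisturbed elimination and could be used for the fit.

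**Working it through.** **The plan's own figure.** The sample size rests on plasma AUC over 24 h: SD 1.37, margin 0.83, 90% confidence. The half-width t(0.95, n−1) × 1.37/√n is 0.849 at n = 9 and 0.794 at n = 10, so 10 per group reproduces. This calculation does not involve λz.

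**Inputs.**
- Half-life 17 h (Background, plasma), so λz = ln 2/17 = 0.0408 per h. The article writes its half-life formula with a base-10 logarithm; that is a separate matter, and the natural logarithm is used here.
- Sampling times from the intensive-phase section, the wash-out section and Table 2.
- Residual SD on the log scale, s: not in the article. Assumed 0.15, range 0.10–0.20, and constant over time.
- Fitting window: not set by the article. 8–24 h is taken as the main case.

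**Span.** 8–24 h is 16/17 = 0.94 half-lives, and 6–24 h is 18/17 = 1.06. The scheduled samples from 24 to 144 h add 120/17 = 7.1.

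**Leverage of the 24 h sample.** For 8, 10, 12 and 24 h the mean is 13.5 and Sxx = 30.25 + 12.25 + 2.25 + 110.25 = 155. Leverage is 1/4 + 10.5²/155 = 0.96, where the maximum is 1. It is 0.87 for 4–24 h, 0.92 for 6–24 h and 0.99 for 10–24 h.

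**Per-subject relative standard error of λz** = s/(√Sxx × λz):

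| Samples used (h) | Sxx | s = 0.10 | s = 0.15 | s = 0.20 |
|---|---|---|---|---|
| 8, 10, 12, 24 | 155 | 20% | 30% | 39% |
| 24, 48, 72 | 1152 | 7% | 11% | 14% |
| 24, 48, 72, 96 | 2880 | 5% | 7% | 9% |

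Starting earlier helps a little: at s = 0.15, 6–24 h gives 26% and 4–24 h gives 23%. Dropping the 24 h sample from the 8–24 h fit leaves Sxx = 8 and raises 30% to 130%.

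**In hours.** In 100,000 simulated profiles with a true half-life of 17 h and s = 0.15, the central 95% of single-subject estimates is 10.8–40.3 h from 8–24 h, 14.0–21.6 h from 24–72 h and 15.0–19.6 h from 24–96 h.

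**Group mean, n = 10, s = 0.15.** Relative SE = √[(between-subject CV² + per-subject SE²)/10]. The between-subject CV of λz is not in the article; 20–40% is assumed.
- CV 20%: √[(0.200² + 0.295²)/10] = 11% from 8–24 h, against √[(0.200² + 0.069²)/10] = 7% from 24–96 h, a ratio of about 1.7.
- CV 40%: √[(0.400² + 0.295²)/10] = 16%, against √[(0.400² + 0.069²)/10] = 13%, a ratio of about 1.2.

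**How late the samples stay usable.** At a 17 h half-life, concentrations at 48, 72, 96, 120 and 144 h are about 38%, 14%, 5%, 2% and 0.8% of the 24 h value. The article gives no quantification limit, so the usable gain may stop at 72–96 h.

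**The case against.** The strongest reply is that the article refers only to the curve, sets no window and does not expressly exclude the washout samples from λz. The choice of points is ordinarily left to an analysis plan, which is not shown here. That stands as a limit on certainty: the restriction is the natural reading, not an explicit one. It does not dispose of the point, because the article goes beyond silence. It names the data set for the non-compartmental analysis, and its wash-out section places the later samples after that sampling is complete.

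The gain is also largest for single subjects, and group summaries benefit much less. That is correct. The estimate further depends on an assumed residual CV, held constant even at low concentrations, and on the 8–24 h window.

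A reader might infer more than the article supports:
- **That the detection window is compromised.** Washout is to be reported from the concentrations actually detected, so it is observed directly and not derived from λz.
- **That AUC extrapolation is affected.** None is planned. AUCτ is trapezoidal, and CL/F is dose over that area.
- **That half-life is biased downward because distribution is incomplete at 8–12 h.** This is possible, but the article gives no duration for a distribution phase, so nothing is claimed here.
- **That group results become four times as precise.** The ratio of about four (30% to 7%) applies to one subject's λz.

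**Conclusion.** The point holds for half-life and V/F. As written, the plan leads to a λz that depends mainly on one late sample, with a per-subject relative standard error of about 20–39%. Samples already scheduled would bring this to 7–14% if quantifiable to 72 h, or 5–9% if quantifiable to 96 h. For a group mean of 10 the improvement is about 1.2- to 1.7-fold. These sizes rest on the 17 h plasma half-life, an 8–24 h window, 10–20% residual CV for the per-subject figures, and 15% residual CV with 20–40% between-subject CV for the group means. The article gives no tenofovir half-life for whole blood or dried blood spots, so the figures apply to plasma.

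Cmin and the Kruskal-Wallis comparison of pre-dose concentrations also do not depend on λz, so the adherence comparison is untouched. The change is worth making because it improves planned descriptive outputs at almost no cost; it does not put the trial's main results in doubt.

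**What to change.** Add one sentence to the Statistical analysis section: λz, half-life and V/F are estimated from the concentrations after the last dose, taking the intensive day together with the scheduled Week 7 washout samples (48 h onward), up to the last quantifiable value, with at least three quantifiable points in the log-linear terminal phase. Leave AUCτ, Cmax, Cmin, Tmax and CL/F as planned. If the sponsor already means to use the washout samples, the same sentence settles the reading.

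The cost is analysis wording only, with no new visit, sample or assay. The small downside is that the number of usable late points will vary between subjects. Some, especially in Group 3, may have too few quantifiable values; their λz, half-life and V/F should be reported as not estimable, with the number of such subjects given by group.

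### The analysis section reports AUCτ without defining τ, while the trial is sized on AUC0-24h; in the two intermittent-dosing groups neither reading of τ makes the stated calculations work

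*Protocol article*

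**What the plan says.** The Sample size calculation section takes plasma exposure over 24 h as its reference: "the precision required is a mean TFV plasma AUC_0-24h_ at steady state within ±25% of the true population mean". Its planning values come from once-daily dosing: "The mean (± standard deviation) TFV AUC_0-24h_ in HIV-infected adults is 3.32 ± 1.37 μg.hr./mL". The same target is applied to every arm: "a sample size of 10 participants is required for each of the 3 groups, making 30 participants in total".

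The Statistical analysis section describes the primary endpoints as descriptive pharmacokinetic endpoints as a class. For plasma and blood it lists AUCτ with Cmax, Tmax, CL/F, V/F and Cmin, and states that "AUCτ will be determined using the linear trapezoidal method". It obtains CL/F as dose over AUC0-τ, and renal clearance as the urinary fraction times CL/F. Neither this section nor the abbreviation list defines τ, and AUC0-24h does not appear in the section.

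The non-compartmental analysis is tied to the intensive sampling at Week 7. For that visit the protocol says: "Venous blood samples are then collected at 1, 2, 4, 6, 8, 10, 12 and 24 h post-dose". The Monday dose sampled there is the last dose in all groups.

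Table 1 sets the schedules: daily in Group 1; Monday, Wednesday, Friday and Saturday in Group 2; Monday and Thursday in Group 3.

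**The concern.** In a once-daily trial AUCτ and AUC0-24h are the same quantity, and the change of label would be harmless. Here the dosing interval is the randomized factor. The intervals are 24 h throughout in Group 1, 48/48/24/48 h over the week in Group 2, and 72/96 h in Group 3. Groups 2 and 3 therefore have no single τ, and the interval that would follow the sampled Monday dose is 48 h or 72 h.

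Two things are at stake. One is the reported exposure. An AUC over the dosing interval reflects the dose divided by clearance almost regardless of how often the tablet is taken, whereas an AUC over a fixed 24 h falls as doses are spaced out. The other is the apparent clearance, which is correct only if the AUC covers the dosing interval. One symbol serves both purposes, and in Groups 2 and 3 no single value of τ suits both.

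**Working it through.** **Sample size, reproduced first.** Inputs: SD 1.37, half-width 0.83 (25% of 3.32), 90% confidence taken as two-sided. Half-width = t(0.95, n−1) × SD/√n.
- n = 9: 1.860 × 1.37/3 = 0.849, above 0.83.
- n = 10: 1.833 × 1.37/3.162 = 0.794, within 0.83.

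So 10 per group reproduces. It refers to AUC0-24h under daily dosing.

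**Inputs for the exposure check.**
- Half-life 17 h (Background), so k = ln 2/17 = 0.0408 per h.
- Dose calendar from Table 1: six weeks, then the Week 7 Monday dose.
- Group 1 AUC0-24h set to the protocol's 3.32 μg·h/mL.
- Assumed: linear one-compartment kinetics with instantaneous input.

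**Formula.** In units of F·Dose/CL, AUC(0–T) = (1 − e^(−kT)) × S, where S is the sum of e^(−k·age) over the Monday dose and all earlier doses.
- 1 − e^(−kT) = 0.624 at 24 h, 0.859 at 48 h and 0.947 at 72 h.
- Group 1: S = 1/0.624 = 1.602.
- Group 2 (earlier doses 48, 72, 120, 168 h old, and so on): S = 1 + 0.141 + 0.053 + 0.008 + 0.001 = 1.203.
- Group 3 (earlier doses 96, 168 h old, and so on): S = 1 + 0.020 + 0.001 = 1.021.

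**Results at 17 h.**

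| | Group 1 | Group 2 | Group 3 |
|---|---|---|---|
| AUC0-24h, ratio to Group 1 | 1.00 | 0.624 × 1.203 = 0.75 | 0.624 × 1.021 = 0.64 |
| AUC0-24h, μg·h/mL | 3.32 | 2.49 | 2.12 |
| AUC over 24/48/72 h, ratio | 1.00 | 0.859 × 1.203 = 1.03 | 0.947 × 1.021 = 0.97 |
| AUC over 24/48/72 h, μg·h/mL | 3.32 | 3.43 | 3.21 |
| CL/F from Dose/AUC0-24h, relative to true | 1.00 | 1/0.751 = 1.33 | 1/0.637 = 1.57 |
| CL/F from Dose/AUC over 24/48/72 h, relative to true | 1.00 | 1/1.033 = 0.97 | 1/0.967 = 1.03 |

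**Sensitivity.**
- With first-order absorption at an assumed 1 per h, AUC0-24h is 1.00/0.74/0.62 and the interval AUC about 1.00/1.04/0.97. The CL/F inflation is then 1/0.740 = 1.35 and 1/0.622 = 1.61.
- Without absorption, over half-lives of 12 to 30 h, the Group 3 ratio runs from 0.75 to 0.48 for AUC0-24h and from 0.99 to 0.92 for the interval AUC. The matching Group 3 CL/F inflation is 1/0.75 = 1.33 to 1/0.48 = 2.08.

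**Data available.** The intensive samples support an AUC to 24 h and no further. Plasma and fingerstick samples on Wednesday and Thursday of Week 7 (about 48 and 72 h) are scheduled under the wash-out phase in Table 2, but the analysis section does not bring them into the non-compartmental analysis.

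**The case against.** The best defence is that τ means 24 h. The visit is headed as a 24-h sampling phase, the trapezoidal rule is given with no extrapolation, and no dose follows the Week 7 Monday dose, so no actual interval follows it. On that reading AUCτ equals AUC0-24h and the exposure gradient is kept. This stands as far as exposure goes. It does not rescue the section, because the same AUC0-τ is then the denominator of CL/F, where 24 h is wrong for Groups 2 and 3.

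A second defence is that a condensed article may leave the definition of τ to the full protocol or analysis plan. That would excuse a missing detail. It does not excuse two differently named exposure measures in adjacent sections, combined with a clearance formula that needs one reading and named samples that support only the other.

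Three further points stand and limit the finding. The sample-size section uses plasma AUC0-24h as a reference value from daily dosing, where the two measures coincide, so the planned number is untouched. The stated between-group test of drug levels is the Kruskal-Wallis comparison of pre-dose concentrations, which does not involve τ. AUC is listed only for plasma and blood, so the urine and oral fluid results do not depend on it.

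A reader might go further and infer that the primary exposure endpoint was switched to one that hides the adherence effect. The document does not support that. It names no single primary exposure endpoint, and the loss of gradient arises only if τ is the dosing interval, which it nowhere says. Nor does it follow that only Group 1 is at steady state. After six weeks of a fixed weekly calendar, a dose one week old contributes e^(−168k) = 0.001 of its initial level, so Groups 2 and 3 are also in a repeating weekly steady state.

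**Conclusion.** The point holds as an undefined and conflicting specification. Read as the dosing interval, AUCτ is not computable in Groups 2 and 3 from the named samples, and if completed it would show almost no difference between groups (1.00/1.03/0.97). Read as 24 h, it matches the sizing measure and keeps the gradient (1.00/0.75/0.64), but apparent clearance is overstated about 1.3-fold in Group 2 and 1.6-fold in Group 3, and renal clearance inherits the error. These sizes rest on linear one-compartment kinetics and the 17 h half-life; the direction is the same across half-lives of 12 to 30 h.

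These parameters are to be reported by group with confidence intervals, so the choice should be written down before analysis. The pre-dose comparison, the washout description and the 10 per group stand as they are.

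**What to change.** In the Statistical analysis section:
- Replace AUCτ with AUC0-24h after the Week 7 Monday dose as the reported exposure measure in all three groups. This matches the sample-size section and the intensive sampling.
- If an interval AUC is wanted, label it by its hours: AUC0-48h in Group 2 and AUC0-72h in Group 3. Compute it with the existing Wednesday and Thursday samples, state that these enter the analysis, and do not read it as the between-group exposure contrast.
- State which AUC enters CL/F in each group, and do not use AUC0-24h in Dose/AUC for Groups 2 and 3. Under the assumptions above, the hour-labelled interval AUC gives CL/F within about 3% of the true value at a 17 h half-life. Renal clearance should use the same CL/F.

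The cost is a wording change and slightly more analysis. The samples are already scheduled, and no participants are added.

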## Abbreviations

ALT: alanine aminotransferase
AMS: Faculty of Associated Medical Sciences
ART: antiretroviral therapy
AST: aspartate aminotransferase
AUC: area-under-the-curve
CI: confidence interval
CL/F: apparent clearance
C_max_: maximum concentration
C_min_: minimum concentration
CPQA: Clinical Pharmacology Quality Assurance
DAIDS: Division of AIDS
DBS: dried blood spots
DOT: Directly Observed Therapy
Fe: fraction of drug excreted unchanged in the urine
FTC: Emtricitabine; GFR, Glomerular filtration rate
NIH: National Institutes of Health
PBMCs: Peripheral blood mononuclear cells
PK: Pharmacokinetics
PrEP: Pre-exposure prophylaxis
TARGET study: Tenofovir Adherence to Rapidly Guide and Evaluate PrEP and HIV Therapy
TDF: tenofovir disoproxil fumarate
TFV: Tenofovir
TFV-DP: TFV-diphosphate
T_max_: time to maximum concentration
V/F: apparent volume of distribution
WHO: World Health Organization
λz: terminal slope

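### The half-life formula uses log10(2) with a slope whose log base is not stated; applied to the usual natural-log λz, it gives TFV half-lives 2.303 times too short

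*Protocol article*

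**What the plan says.** The Statistical analysis section of the Protocol article describes a non-compartmental analysis of the Week 7 intensive sampling, with parameters reported for plasma and for venous and fingerstick blood. On the terminal phase it says "The terminal slope (λz) will be determined from the log-linear portion of the curve" and then that "the half-life will be calculated as Log_10_ (2)/λz". The Abbreviations section adds only "λz: terminal slope". Neither place gives the base of the logarithm used for the slope.

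V/F is among the parameters to be reported, but no formula is given for it. Clearance has one, which does not involve λz: "Total body clearance (CL/F) will be calculated using Dose/AUC_0-τ". Half-life is not in the list of parameters, although the section does say it will be calculated.

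For scale, the Background section states that "TFV has a plasma elimination half-life of 17 h".

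**The concern.** For mono-exponential decline, C = C0·exp(−λz·t), and the concentration halves after ln(2)/λz. The printed numerator is log10(2). The subscript 10 is explicit, so this is not an ambiguous use of the word log. A log10 numerator is right only with a slope taken on log10 concentrations, and that slope is not the rate constant that λz normally denotes.

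The primary endpoints are descriptive pharmacokinetic ones, so the printed formulas are a large part of the analysis plan. A half-life calculated as written from a natural-log slope would be wrong by the same factor in every participant and group. It could not be compared with published values such as the 17 h that the article itself cites.

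**Working it through.** The article reports no number derived from the half-life formula, so there is no figure of its own to reproduce. The check is algebra with a noise-free illustration.

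**Inputs**
- Half-life formula: log10(2)/λz (Statistical analysis).
- Base of the slope: not stated (Statistical analysis; Abbreviations).
- Illustrative true half-life: 17 h (Background).
- Illustrative clearance: the 300 mg TDF dose divided by the AUC in the Sample size calculation section, "The mean (± standard deviation) TFV AUC_0-24h_ in HIV-infected adults is 3.32 ± 1.37 μg.hr./mL". Since 3.32 μg·h/mL = 3.32 mg·h/L, CL/F = 300/3.32 = 90.36 L/h.
- V/F = (CL/F)/λz: the usual non-compartmental form, assumed here.

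**Constants**
- ln(2) = 0.6931 and log10(2) = 0.3010.
- Ratio: 0.6931/0.3010 = 2.303; inverse 0.434.

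**Slopes for a true half-life of 17 h**
- Natural-log slope: 0.6931/17 = 0.04077 per h.
- Log10 slope: 0.04077/2.303 = 0.01771 per h.

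**Half-life and V/F under each reading of λz**

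| Scale of λz | Printed formula, 0.3010/λz | ln(2)/λz | (CL/F)/λz |
|---|---|---|---|
| Natural log, 0.04077/h | 7.38 h (wrong) | 17.0 h (right) | 2216 L (right) |
| Log10, 0.01771/h | 17.0 h (right) | 39.1 h (wrong) | 5103 L (2.303 times too large) |

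The factor of 2.303 does not depend on the half-life, dose or AUC chosen. The litre and hour figures are illustrations only.

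**V/F by the other route**

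V/F can also be obtained as (CL/F) × t1/2/ln(2).
- Log10 slope, printed formula, t1/2 = 17.0 h: 90.36 × 17.0/0.6931 = 2216 L. Half-life and V/F are then both right.
- Natural-log slope, printed formula, t1/2 = 7.38 h: 90.36 × 7.38/0.6931 = 962 L. V/F is then 2.303 times too small.

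Whether V/F is affected therefore depends on two things the article leaves open: the scale of the slope and the formula for V/F.

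**What does not use the formula**
- AUCτ comes from the trapezoidal rule; Cmax, Cmin and Tmax are read from the data.
- CL/F is dose over AUC. The urinary fraction is amount excreted over dose, and renal clearance is that fraction times CL/F.
- The Kruskal-Wallis tests compare demographic variables and pre-dose concentrations.
- The sample size rests on the mean and standard deviation of AUC.

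**The case against.** The strongest reply is that one reading contains no numerical error. The article calls λz only a terminal slope. If that slope is fitted on a log10 plot, the printed half-life formula is exactly right, and if V/F is then derived from the half-life, V/F is right too. This stands. A reader might infer that some parameter must be wrong whichever way λz is read, but the article does not support that, because the V/F error needs a V/F formula that it does not give.

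A second reply is that this is probably a slip of notation. The same section prints RDF where TDF is evidently meant. Stata is assigned only to the non-pharmacokinetic analyses, so the pharmacokinetic tool is not named, and standard software would normally apply ln(2). This also stands as far as it goes: one cannot say that every reported half-life will be wrong, only that it will be if the sentence is applied as written to a natural-log slope. It does not make the sentence correct.

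A third reply concerns reach. A reader might infer that the error carries into the washout results, the period over which a dose can be detected, or the adherence benchmarks. It does not. The Statistical analysis section reports washout from concentrations measured after the last dose. The Abstract and Discussion describe the benchmarks as concentration thresholds. The Randomization section bases the 4-week washout on half-lives already reported, not on this calculation. No half-life calculation is described for urine or oral fluid.

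**Conclusion.** The point holds in limited form. The article prints a half-life formula that is wrong under the standard meaning of its own symbol, and nothing in it corrects the formula or states the scale of the slope. Because a formula is printed, this is a misstatement and not a detail left to a fuller document.

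- With λz as the natural-log rate constant, and the formula applied as written, plasma and blood TFV half-lives come out 2.303 times too short.
- With λz as a log10 slope, the half-life is right. V/F is 2.303 times too large only if it is computed as (CL/F)/λz with that slope.

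The error touches half-life and, conditionally, V/F. The main exposure and concentration results stand, as do the group comparisons and the sample size. It should be corrected before the pharmacokinetic analysis is run, but it gives no reason to doubt the design.

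**What to change.** Replace the sentence with three linked definitions:

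- λz is the negative slope of the regression of ln(concentration) on time over the terminal phase.
- t1/2 = ln(2)/λz.
- V/F = (CL/F)/λz, using the same λz.

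This costs one line of wording. No design, sampling or sample-size change follows. If a half-life or V/F has already been computed, confirm which slope and numerator were used; any correction is multiplication or division by 2.303.

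### As written, Fe divides several days of multiple-dose urine by one dose and CLR divides that urine by a 24-h AUC, so CLR is overstated on the plain reading and Fe differs falsely between groups

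*Protocol article*

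**What the plan says.** All three definitions stand in the Statistical analysis section of the protocol article.

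- Fe is the "total amount of TFV excreted during the urine collection period following cessation of RDF divided by the dose" (RDF is evidently a misprint for TDF).
- "Total body clearance (CL/F) will be calculated using Dose/AUC_0-τ".
- "The renal TFV clearance (CLR) will be calculated by multiplying Fe_TFV_ and CL/F".

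The same section bases the non-compartmental analysis on "TFV concentration data generated from the intensive blood samplings at Week 7".

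The sampling is described elsewhere. Under the intensive 24-h PK phase, the Monday dose of Week 7 is final: "This is the last dose of Truvada® for all subjects". Plasma sampling for that phase ends at 24 h: "Venous blood samples are then collected at 1, 2, 4, 6, 8, 10, 12 and 24 h post-dose". On the same day, "Urine samples are collected pre-dose and over the intervals of 0–4 h, 4–8 h, 8–12 h, and 12–24 h". Under the 4-week wash-out phase, "subjects return to the clinic once a day for the remaining 5 days of Week 7 for blood, urine (24-h) and oral fluid specimen collection". The same is shown in Table 2, which marks 24-h urine at both the PK visit and the Week 7 washout visits.

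No hours are attached to the urine period in the Fe definition, and no step subtracts drug remaining from earlier doses.

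**The concern.** A renal clearance calculated as amount over AUC is valid only if both terms cover the same interval. Here the urine term appears to cover six days and the plasma term one.

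Fe has a separate problem. After six weeks of dosing, urine collected after the last tablet also contains drug from previous tablets, yet the total is divided by a single dose. The excess depends on how recently the previous tablets were taken, and that is what the randomization varies. A property of drug elimination would then seem to change with adherence level, when the cause is only the schedule. Urine is one of the matrices the trial sets out to characterize, so a reader of the results could take such a gradient as real.

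**Working it through.** The article states no value of Fe or CLR, so there is no figure to reproduce. The check applies its definitions to its own schedule.

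**Inputs**
- Half-life 17 h (Background), so k = ln 2/17 = 0.0408 per h.
- AUC window 0–24 h (intensive PK phase).
- Urine window 24 h on the PK day plus 5 × 24 h = 144 h, taking each of the five daily returns as the preceding 24 h.
- Dosing days (Table 1): Group 1 daily; Group 2 Monday, Wednesday, Friday, Saturday; Group 3 Monday, Thursday. Before the final Monday dose, the previous dose was 24 h, 48 h and 96 h earlier respectively.
- Assumed: linear one-compartment kinetics and the same true Fe in all groups.

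**CLR**

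CLR = (Ae/Dose) × (Dose/AUC) = Ae(urine period)/AUC(0–24).

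Bias = (1 − e^(−144k))/(1 − e^(−24k)) = 0.997/0.624 = 1.598.

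This is the same in every group. For assumed half-lives it is 1.33 (12 h), 1.44 (14 h), 1.76 (20 h), 1.97 (24 h) and 2.27 (30 h). Adding first-order absorption at an assumed 1 per h gives 1.62 to 1.64 at 17 h.

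**Fe**

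Let S be the drug in the body just after the last dose, in units of one dose, found by adding what remains of every earlier dose.

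- Group 1: 1/(1 − e^(−24k)) = 1/0.624 = 1.602.
- Group 2: 1 + e^(−48k) + e^(−72k) + e^(−120k) + e^(−168k) + … = 1 + 0.141 + 0.053 + 0.008 + 0.001 + … = 1.203.
- Group 3: 1 + e^(−96k) + e^(−168k) + … = 1 + 0.020 + 0.001 + … = 1.021.

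Fe bias is S × (e^(−ak) − e^(−bk)) for urine collected from a to b hours:

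| Urine window | Fe, Group 1 | Fe, Group 2 | Fe, Group 3 | CLR |
|---|---|---|---|---|
| 0–144 h | 1.60 | 1.20 | 1.02 | 1.60 |
| 0–24 h | 1.00 | 0.75 | 0.64 | 1.00 |
| 24–144 h | 0.60 | 0.45 | 0.38 | 0.60 |

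The window multiplies all groups equally, so the ratio of Group 1 to Group 3 is 1.602/1.021 = 1.57 in every row. Choosing a window can repair CLR but cannot remove the Fe gradient.

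**CL/F**

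Dose/AUC(0–24) is biased by the inverse of the 0–24 h row: 1.00, 1.33 and 1.57. Over 0–144 h the Fe and CL/F biases multiply to the common CLR figure, for example 1.20 × 1.33 = 1.60 in Group 2.

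**Early distribution phase**

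Suppose a fast phase, gone by 24 h, carries a fraction f of single-dose AUC (f is assumed; the article gives none). Group 1 CLR bias becomes 1 + 0.598(1 − f): 1.42 at f = 0.3 and 1.30 at f = 0.5. At f = 0.3, CLR bias is about 1.42, 1.38 and 1.36 across groups, and 0–144 h Fe is 0.3 + 0.7 × (1.598, 1.200, 1.018) = 1.42, 1.14 and 1.01.

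**Does a corrected AUC work?**

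Take AUC(0–24) + (C24 − Cpre)/λz, in units of the single-dose AUC. Here C24/λz = 0.376 × S and Cpre/λz = S − 1.

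- Group 1: 1.000 + 0.602 − 0.602 = 1.00.
- Group 2: 0.751 + 0.452 − 0.203 = 1.00.
- Group 3: 0.637 + 0.384 − 0.021 = 1.00.

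**The case against.** The strongest reply is that the article gives no hours. The PK-day urine is a self-contained 0–24 h collection, and if that was meant, CLR is right. A journal article may leave such detail to the full protocol. This stands as far as the 60% goes: it is conditional on the window, and a washout-only window would make CLR about 40% too low instead. It does not rescue the Fe formula, which the article states outright and which misleads under all three windows.

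Second, the size depends on the model. A distribution phase shrinks the bias and makes it slightly unequal across groups. That also stands; the direction does not change.

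Three stronger inferences are not supported.

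- A reader might infer that CLR itself shows a marked adherence gradient. Under one-compartment decay its inflation is the same in every group; the gradient belongs to Fe and, separately, to CL/F.
- A reader might infer that the TDF tablet mass will be divided into a TFV amount without conversion. The article says only that the dose is used and is silent on units, so no error can be shown.
- A reader might infer that the trial's main conclusions are at risk. The Discussion frames the aim around concentrations, the planned group test on drug data concerns pre-dose concentrations, and no comparison of Fe between groups is planned.

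**Conclusion.** The definitions are wrong as written and should be corrected before analysis. On the plain reading (0–144 h urine, 0–24 h AUC), with one-compartment decay at 17 h, CLR is overstated about 1.6-fold. The range is 1.33 to 2.27 for assumed half-lives of 12 to 30 h, and the bias is smaller if an early phase carries part of the AUC. On the same assumptions Fe is about 1.60, 1.20 and 1.02 times the truth in Groups 1, 2 and 3. The CLR error disappears if 0–24 h urine was intended; the false Fe gradient does not.

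The consequence is limited to Fe, CLR and CL/F, which are descriptive parameters. The raw data, the sample size and the pre-dose comparisons are untouched.

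**What to change.** Replace the Fe, CL/F and CLR definitions with the following.

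- CLR = Ae(0–24)/AUC(0–24), from the PK-day urine intervals and plasma.
- Corrected AUC = AUC(0–24) + (C24 − Cpre)/λz, in every group. This adds the tail of the last dose and removes carry-over.
- CL/F = Dose/corrected AUC.
- Fe = CLR × corrected AUC/Dose. In Group 1 at steady state C24 = Cpre, so this reduces to Ae(0–24)/Dose.
- Use the later 24-h urines for the washout curve only.

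State the hours of each window. State also that λz is the slope on the natural-log scale, since the same section's half-life formula uses a base-10 logarithm.

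The cost is a few lines of analysis text and no new samples. The small downside is that the correction depends on an estimated λz.
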